#### 2.2.2 Study population. inclusion and exclusion criteria

In this research, we are consecutively recruiting a sample of eligible 2,250 children across the region (1,500 children aged 1 day to 18 years suspected of IEM and 750 healthy children to set the reference values). Western Kazakhstan is divided into four regions (provinces, oblasts) according to the administrative division: Aktobe, West Kazakhstan, Atyrau, and Mangystau (Figure 2).

**FIGURE 2 F2:**
[figure not shown]
Sites for data collection throughout western Kazakhstan.

Children from the western Kazakhstan population with suspected metabolic disorders are examined for congenital metabolic disorders and referred by primary care neonatologists and pediatric consultants between October 2022 and August 2024 based on their clinical symptoms associated with metabolic disorders. The study includes newborns and children being treated in maternity wards and pediatric clinics of 7 pediatric hospitals in the region. Patients with suspected IEM from all sites are referred to the Regional Tertiary Care Center or the Mother and Infant Health Center in Aktobe, or their samples are sent from other involved hospitals. Patient information is obtained from the Individual Registration Cards (IRCs) completed by study participants. The completed questionnaires are checked by the researchers. In case of improper collection, data must be removed from the study if it is impossible to check adequately. The IRC sample and other supplementary materials are placed in the *clinical. trials.gov* Register (https://www.clinicaltrials.gov/study/NCT05910151) and a publicly available repository (https://osf.io/cmrh7/).

To set reference values of 15 AAs, 35 ACs, and SuAc, healthy participants without any disease are included in the study. A total of 750 healthy male and female children aged 1 day to 18 years are recruited based on random selection. Participants will be balanced by gender and place of residence. Considering the distribution of urban and rural populations in western Kazakhstan, approximately half of them will be selected in urban areas, the other half in rural areas. A summary of the age, gender, and geographic distribution of study participants will be presented in Table 1.

**TABLE 1 T1:** Demographic data to be collected on study participants.

Variables	Selective screening (n = 1,500)	Healthy children (n = 750)
Age in days, years (median, range)		
Weight in grams, kilograms (median, range)		
Gender		
Male, n		
Female, n		
Geographic distribution		
Aktobe province		
Atyrau province		
West Kazakhstan province		
Mangystau province		
Urban population		
Rural population		

Screened children with positive first-level LC-MS/MS test results will be referred for second-level screening.

#### 2.2.3 Criteria for inclusion of healthy children in the study (to set reference values)

Pediatricians examine all children in this study to ensure they do not suffer from any disorder or chronic disease. Healthy male and female newborns born after an uncomplicated pregnancy and vaginal delivery should have a body weight of 2,500–4,000 g, gestational age of 37–42 weeks, and an APGAR score greater than 7 in 10 min after birth. None should be diagnosed with birth asphyxia, defined as an Apgar score ≤6 at 5 min. All newborns must be breastfed, and their mothers must be healthy persons aged between 24 and 36. They must not have any food restrictions (vegetarian, vegan, etc.). Echograms of the placenta and fetus, as well as laboratory tests, should be normal throughout pregnancy.

#### 2.2.4 Criteria for inclusion in the selective screening for IEM

Children from 1 day to 18 years of age will be enrolled for selective screening for IEM if one of the main criteria or two or more additional criteria (symptoms) are identified. The inclusion criteria for IEM selective screening are presented in Table 2.

**TABLE 2 T2:** Criteria for inclusion in the selective screening for IEM.

Main criteria (symptoms)	Sudden deterioration in the clinical condition of the child after a period of normal development (days, weeks, months): Acute metabolic encephalopathy lethargy (coma) seizures resistant to antiepileptic therapy
	Hepatomegaly (hepatosplenomegaly)
	Metabolic acidosis with increased anion gap
	Multiple fractures
	Child mortality in the family from diseases with similar symptoms
Additional criteria (symptoms)	Treatment-resistant seizures
	Abnormal muscle tone: dystonia, hyperkinesis, hypotension
	Speech retardation
	Mental retardation of unknown cause
	Cardiomyopathy
	Tachypnea
	Frequent spitting up (vomiting)
	Osteoarticular anomalies (joint stiffness, chest deformity, rickets-like changes)
	Hernias (umbilical, inguinal-scrotal)
	Persistent or recurrent hypoglycemia
	Metabolic alkalosis
	An increase in ketone bodies in the blood and (or) urine
	Hyperammonemia
	An increase in the level of liver enzymes (ALAT, AST) more than 1.5 times
	Increase in the level of creatine phosphokinase (CPK) by more than 2 times
	Decrease in the level of alkaline phosphatase (AP) below the age norm
	Imaging or electrophysiological examinations indicating a metabolic disorder
	Leukopenia
	Thrombocytopenia
	Abnormal odor of urine, body, earwax, any unusual odor
	Hair growth disorders, alopecia
	Ophthalmic anomalies
	Unusual appearance, dysmorphic features
	History of death of a previous sibling of unknown cause
	Parents’ consanguinity
	Positive family history with metabolic disorders

Exclusion criiteria:

Patients having the following conditions will be excluded:1. Perinatal brain injury,2. Brain injury,3. Infections of the central nervous system,4. Toxicological diseases,5. Tumors,6. Chromosomal abnormalities,7. Symptoms specified in the Inclusion criteria, but with a confirmed diagnosis of any disease other than Amino acid disorders (AAD), Fatty acid oxydation disorders (FAOD), or Organic acidemias (OA).

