The efficacy and risks of expanded newborn screening for IEM require careful evaluation before it can be accepted as a mandatory national program. The lack of epidemiological data on the incidence of IEM is one of the reasons for the delay in the development of proper population-based newborn screening for IEM using the LC-MS/MS method in Kazakhstan. Currently, NBS is being conducted in Kazakhstan for two hereditary diseases - phenylketonuria (PKU) and congenital hypothyroidism, the most represented screening diseases in most countries (Therrell and Padilla, 2018). This nationwide NBS program based on biochemical tests started in 2007 (Loeber et al., 2021), long after NBS was introduced in the United States in 1963 (Guthrie and Susi, 1963). Besides, in Kazakhstan, before the present study, state-funded MS/MS selective screening programs were implemented as sporadic pilot projects in some regions of the country without completion. Reports on these projects have not been published in peer-reviewed journals. As MS/MS neonatal screening is not mandatory in Kazakhstan, there are no uniform technical specifications for IEM screened by MS/MS in pilot studies. Hence, data on the frequency of IEM at the national level are not presented. For a country with no mandatory ENBS MS/MS program, selective screening can become essential for diagnosing IEM. The present research aims to develop and validate the LC-MS/MS method for simultaneously determining 51 metabolites in dry blood spots for IEM screening, as well as clarifying age-related ranges for AAs, ACs, and SuAc in Kazakhstan children. It is commonly accepted that children need to use reference populations that reflect changes associated with growth and development (Dogan et al., 2017). Therefore, one of the objectives of this study is to set reference intervals for the concentration of amino acids, succinylacetone, and acylcarnitines in dry blood spots for different age groups in the range from 1 day to 18 years. Owing to historically established social-cultural traditions supported by the legislation, consanguineous marriages are practically absent in Kazakhstan. This distinguishes Kazakhstan from many Asian and European countries, where consanguineous marriages are a real problem and, according to researchers, they are one of the reasons for the relatively high incidence of certain groups of IEM identified during selective newborn screening (Nagaraja et al., 2010; Al Riyami et al., 2012; Golbahar et al., 2013; Selim et al., 2014; Hassan et al., 2016; Demirelce et al., 2020; Gayduk et al., 2022; Magdy et al., 2022).

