Indices of sensitivity (Sn), specificity (Sp), positive predictive values (PPVs), and negative predictive values (PVN) will be calculated for each diagnostic test under consideration. PPVs will be calculated by dividing the total number of true positive cases by the total number of true positive and false positive cases. The detection rate will be calculated by dividing the number of cases diagnosed by the number of screened children with suspected metabolic disorders. Multiple linear regression coefficients will be calculated to assess the relationship of each analyte with the factors of gender, weight, and place of residence. Due to the number of variables subjected to analysis, and the anticipated presence of multiple outcomes, the included tests may not be sufficient. So, the cluster analysis and, possibly, the decision-tree method will be applied. Decision trees break down complex data into more manageable parts, beneficial in prediction analysis, data classification, and regression. A dimensionality reduction method, principal component analysis (PCA), will also be applied. Two-sided levels <0.05 are assumed to be statistically significant. Statistical analysis will be carried out using the statistical packages IBM SPSS v. 23.0 (IBM, Armonk, NY, United States), Statistica (StatSoft, Inc., Tulsa, OK, United States, v. 10), and R 3.3.2 (R Foundation for Statistical Computing, Vienna, Austria.)

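### Children with an already confirmed target disorder are not barred or counted separately, and PKU incidence is to be taken from selective screening although newborns are already screened for PKU

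*Protocol article*

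**What the plan says.** **Eligibility.** Section 2.2.4 opens with "Children from 1 day to 18 years of age will be enrolled for selective screening for IEM", given one main or at least two additional criteria from Table 2. Exclusion 7 then removes children who have such symptoms but "with a confirmed diagnosis of any disease other than Amino acid disorders (AAD), Fatty acid oxydation disorders (FAOD), or Organic acidemias (OA"). No entry or exclusion criterion requires that a child has no earlier diagnosis of a target disorder. Section 2.2.2 describes the cohort in terms of suspicion: "Children from the western Kazakhstan population with suspected metabolic disorders are examined for congenital metabolic disorders".

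**Detection rate.** Section 3.2 states: "The detection rate will be calculated by dividing the number of cases diagnosed by the number of screened children with suspected metabolic disorders". It also plans positive predictive values as true positives over all positives. Table 5 (section 3.3) lists positive cases among the 1,500 with no column for new versus previously known.

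**PKU.** The Introduction states: "Currently, NBS is being conducted in Kazakhstan for two hereditary diseases - phenylketonuria (PKU) and congenital hypothyroidism". It adds: "This nationwide NBS program based on biochemical tests started in 2007". It also names PKU as the exception to the lack of national prevalence data. PKU is nevertheless the first target disease in Table 3.

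**Incidence.** Section 3.4 plans incidence for each disease, and for each of the AAD, OA and FAOD classes, over births in the region in 2023–2024. Section 4 repeats this and plans to set each frequency beside incidence data from other parts of the world.

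**The concern.** A detection rate for selective screening should measure how often testing finds a target disorder in children not yet known to have one. Exclusion 7 treats the two kinds of prior diagnosis differently. A confirmed non-target disease removes the child, while a confirmed target disease does not. Since nothing downstream separates new from known, an earlier diagnosis can be reported as a detection, and it can enter the positive predictive value as a true positive.

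The PKU problem does not depend on that wording. The study finds cases only through symptomatic referral, while a separate programme tests newborns for PKU. A child found at birth may never be referred with Table 2 symptoms and so is missed. Or the child is referred as a known patient, and counting that child as a detection is wrong. Neither count, divided by births, is the incidence of PKU. The AAD class total inherits the fault.

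The results have uses. Section 1 hypothesises lower frequencies than in populations practising consanguineous marriage, and missed PKU cases would lean towards that hypothesis. Section 4 says the content of a future newborn panel will depend on the frequencies found.

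**Working it through.** **Inputs from the protocol article**
- Screened children: n = 1,500 (section 2.2.1).
- Planning frequency: p = 2% to 2.5% (section 2.2.1).
- Live births per year: 69,000 to 73,000 (section 2.2.1).
- PKU rates quoted for other populations: about 1:10,000, 1:50,000 and 1:110,000 (section 4).

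**Input not in the documents**
- Number of previously confirmed cases enrolled, k. Assumed range: 0 to 20.

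**Step 1: cases implied by the plan.** 1,500 × 0.02 = 30 and 1,500 × 0.025 = 37.5. The plan states no target precision, so 1,500 cannot itself be re-derived. The 95% half-width it implies is 1.96 × √[p(1 − p)/1,500], which is 0.71 points at 2% and 0.79 points at 2.5%.

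**Step 2: effect of k known cases on the detection rate.** If the remaining 1,500 − k children have frequency p, and the k known cases are counted as diagnosed:

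observed rate = [p(1,500 − k) + k] / 1,500, an increase of k(1 − p)/1,500.

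| k (assumed) | p = 2% | p = 2.5% | Ratio to p |
|---|---|---|---|
| 0 | 2.00% | 2.50% | 1.00 |
| 2 | 2.13% | 2.63% | 1.05–1.07 |
| 5 | 2.33% | 2.83% | 1.13–1.16 |
| 10 | 2.65% | 3.15% | 1.26–1.33 |
| 20 | 3.31% | 3.80% | 1.52–1.65 |

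For k = 10 the increase is 10 × 0.98/1,500 = 0.65 points at 2%, and 10 × 0.975/1,500 = 0.65 points at 2.5%. That is close to the whole half-width from step 1.

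**Step 3: positive predictive value.** With TP true and FP false positives, k known cases that test positive change TP/(TP + FP) to (TP + k)/(TP + k + FP). This is larger whenever FP and k are above zero. The size cannot be given without TP and FP.

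**Step 4: sensitivity of PKU incidence to one child.** Two years of births are 2 × 69,000 = 138,000 to 2 × 73,000 = 146,000. One child missed or wrongly counted moves the estimate by 1/146,000 to 1/138,000, or 0.68 to 0.72 per 100,000. As a yardstick only, 1:110,000 is 0.91, 1:50,000 is 2.0 and 1:10,000 is 10 per 100,000. One child is thus 75–80% of the lowest quoted rate (110,000/146,000 to 110,000/138,000) and about 7% of the highest. The documents do not say which of these rates, if any, applies in western Kazakhstan.

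**Step 5: direction.** Children found at birth and never referred lower the study's PKU count. Known children who are referred and counted raise it. The documents give no number for either group, so the net sign is open.

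**The case against.** The strongest reply is that the cohort is described throughout as children with a suspected disorder: in the abstract, sections 2.2.2 and 3.2, and the title of Table 5. A child with a confirmed disorder is not ordinarily called suspected, and entry also needs Table 2 symptoms. On that reading, exclusion 7 only says that a target disease is not a competing diagnosis. This stands in part. It makes enrolment of known cases uncertain, so the results cannot be called biased outright. It does not close the gap, because no criterion bars such children and no table separates them.

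A reader might infer that exclusion 7 also drops children whose work-up ends in another diagnosis, which would shrink the denominator. The text does not support this. Eligibility criteria normally apply at entry, and the only later removal described (section 2.2.2) concerns improperly collected data. Section 3.2 divides by children screened, and Table 5 is built on 1,500.

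A reader might also infer that nearly all study-age children with PKU are already known. The Introduction gives a nationwide programme and a start year, but no coverage or sensitivity. Children aged up to 18 recruited from 2023 include some born before 2007 (2023 − 18 = 2005).

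Nor can it be concluded that the detection rate is incomparable with the 1.2% and 9.2% cited in section 2.2.1, because those studies' eligibility rules are not shown.

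Finally, section 4 concedes that a thorough assessment of prevalence needs expanded newborn screening, and it speaks of relative frequencies. That caveat is fair, but the same section keeps the per-disease incidence over births and the international comparison.

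**Conclusion.** The point holds in two limited parts.

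First, the criteria allow children with a previously confirmed AAD, FAOD or OA, and the planned outputs cannot tell them from new detections. The detection rate and positive predictive value can therefore be inflated. Under the planning frequency and an assumed 10 known cases all counted as diagnosed, the detection rate rises by about 0.65 points. With none enrolled there is no inflation. The actual number is not in the documents.

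Second, PKU incidence, and AAD incidence that includes PKU, is not valid as selectively detected cases over 2023–2024 births while a nationwide newborn programme finds PKU separately. This rests on the protocol's own account of that programme and holds even if no known case is enrolled. The direction and size of the error are not determined.

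No figure stated in the protocol is shown to be wrong. The matter can still be put right in the analysis if prior-diagnosis status is recorded.

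**What to change.** 1. State that exclusion 7 applies to diagnoses confirmed before the blood spot is taken. Keep every screened child in the denominator, including those later given another diagnosis.
2. Record for each child whether an AAD, FAOD or OA was confirmed before enrolment. Leave those children out of the detection rate and positive predictive value, and list them separately beside Table 5.
3. Report PKU from this study only as cases not found by newborn screening. Take PKU incidence from the newborn programme, and show AAD results with and without PKU, including in the international comparison.

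The cost is one clarified eligibility sentence, one data field and slightly fewer counted cases. The registration card is posted outside the article, so whether it already captures prior diagnosis cannot be judged here. If it does, only the reporting changes.

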### 2.3 Methods and procedures

#### 2.3.1 Mass spectrometry analysis. specimen collection and storage

Neonatal whole blood samples are taken from high-risk and healthy infants no earlier than 3 h after feeding by heel prick with a heel stick. Five drops of whole blood (∼75 µL each) are put onto Guthrie cards, Ahlstrom 226 filter paper, PerkinElmer 226 Five-Spot Card (PerkinElmer Health Sciences, Greenville, United States) to form dry blood spots (DBSs) for LC-MS/MS analysis. The sample must be taken before transfusion therapy or extracorporeal membrane oxygenation. If the sample was not taken before the administration of transfusion agents, blood should be taken no earlier than 48–72 h after the transfusion.

Whole blood samples from older children at high-risk and healthy children are collected after 4-hour fasting using a standard venipuncture method. The DBS card is prepared by applying five drops of whole blood (each ∼75 μL) to the Guthrie cards, Ahlstrom 226 filter paper, PerkinElmer 226 Five-Spot Card (PerkinElmer Health Sciences, Greenville, United States).

Samples must be dried for 4 h at room temperature and then stored at 4°C in individually labeled zippered plastic bags with desiccants or other sealed containers until analyzed by LC-MS/MS by standards of the Institute of Clinical and Laboratory Standards (CLSI, 2013). Samples must be sent to the laboratory within 5 days. In case of long-term storage of samples, it will be carried out at a temperature of −20°C. Cut-off values will be set according to the manual for the Neobase2 TM Non-derivatized MSMS kit (PerkinElmer, Wallac Oy, Turku, Finland). They will be adjusted over time as the number of samples increases.

If metabolite concentrations in dry blood spot samples exceed the cut-off values, the LC-MS/MS test will be repeated using the same dried blood spot sample the next day. If the test results show persistent abnormal results, the child will be further examined. Blood and urine are used to confirm the diagnosis. Diagnosis is confirmed by urine organic acid analysis, plasma amino acid analysis, or direct enzyme analysis. Duplicate samples are stored frozen at −20°C with a desiccating agent.

#### 2.3.2 Specimen preparation and LC-MS/MS analysis

The Neobase2 TM Non-derivatized MSMS kit (PerkinElmer, Wallac Oy, Turku, Finland) is used to quantify 15 amino acids, free carnitine, 35 acylcarnitines, and succinylacetone in dried blood spots according to the manufacturer’s instructions.

The vial with lyophilized isotope-labeled internal standards (IS) is recovered by adding 1.4 mL of the extraction solution that is included in the Neobase 2 kit. The Extraction Working Solution (EWS) IS prepared by diluting the recovered internal standards with the extraction solution 1:100 (v/v) and 1: 50 (v/v) for SUAC.

Dried blood samples are analyzed using Shimadzu LCMS-8050 Triple Quadrupole Mass Spectrometer (Shimadzu Corporation, Kyoto, Japan). Level I and Level II (low standard and high standard) dried blood drops are included in each assay lot of the Neobase2 TM Non-derivatized MSMS kit to monitor system accuracy and precision.

To analyze amino acids, acylcarnitines, and succinylacetone, stored DBS card samples must be brought to room temperature (+18 to +25°C) before extraction. A 3.2 mm disc (equivalent to ∼3.1 µL of whole blood) is punched out of one dried blood spot with a diameter of 3.2 mm using a Wallac DBS Puncher (PerkinElmer, Wallac Oy, [name]) into the well of the 96-well polystyrene U-bottom microplate supplied with the Neobase2 TM Non-derivatized MSMS kit. After adding 125 μL of working extraction solution to each well of the microplate, the plate is covered with an adhesive aluminum film and incubated for 30 min at room temperature on a microplate shaker with a shaking speed of 650 rpm. After incubation, 100 μL of the supernatant is transferred to a new 96-well U-bottom microplate, covered with aluminum foil to reduce evaporation and incubated for 1 h. Then, the plate is placed into the Shimadzu LCMS-8050 Triple Quadrupole Mass Spectrometer autosampler, and 5 μL of supernatant is injected into the LCMS for analysis.

Liquid chromatograph-mass spectrometer Shimadzu LCMS-8050 (Shimadzu Corporation, Japan) used for MS/MS analysis is equipped with a binary pump, an autosampler, and an electrospray ionization source (ESI). Samples are introduced into the LC-MS/MS system through an ESI source for atmospheric pressure ionization, and analysis of the samples is performed using electrospray ionization flow analysis and tandem mass spectrometry (FIA-ESI-MS/MS).

#### 2.3.3 Data acquisition and processing

A program for the LC-MS/MS solvent pump (included) is being set to deliver a mobile phase at a constant flow rate of 150 *μ*L/min, and data are collected in Positive Ion Multiple Reaction Monitoring (MRM) mode. LC-MS/MS ionization source parameters: interface voltage 4.5 kV, interface temperature 250°C, dissolution line temperature 250°C, heating block temperature 400°C, atomizing gas flow 3.0 L/min, and drying gas flow 15.0 L/min. Argon is used at a pressure of 230 kPa as a collision gas. Lab Solution software (version 5.82 SP1, Shimadzu Corporation, Kyoto, Japan) is applied for data collection. Amino acid and acylcarnitine levels will be automatically calculated according to the set internal standards using the Neonatal Solution software (version 2.20, Shimadzu Corporation, Kyoto, Japan). The total running time for each sample is 1.5 min; data is recorded within 0.9 min. The quality control samples supplied with the Neobase2 TM Non-derivatized MSMS kit are extracted and analyzed in parallel with the samples of healthy controls and patients to check the reliability of the data generated by the LC-MS/MS analysis.

